### Primary efficacy outcome measures

The reduction rate of the HAMD 24 score both in overall and in each subset item is defined as (Scores of each evaluation time point − baseline scores)/Baseline scores.

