**Methods:**

This is a single-center, randomized, double-blind, placebo-controlled pilot study. A total of 42 patients will be divided randomly into three groups. Patients will receive an intravenous administration of ATP or PCr or saline twice daily combined with orally administered fluoxetine (20 mg/day) for the first 2 weeks and fluoxetine monotherapy for the following 4 weeks. Follow-up assessment will be completed at week 10. Feasibility outcomes will include percentages of patient eligibility, intention to use medication, willingness to participate, drug adherence, completion of the scheduled assessment, retention, drop-out, etc. Physical examination results, Side Effect Rating Scale, adverse events, results from blood tests, electroencephalogram, and electrocardiograph will be recorded for safety evaluation of the augmentation therapy. The trends of efficacy will be evaluated by the reduction rate of the Hamilton Depression Rating Scale, the mean change of the Clinical Global Impression Scale, and the Patients Health Questionaire-9 items.

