### Study efficacy outcomes

The efficacy outcome measure will be assessed by both clinician-rated HAMD-24, Clinical Global Impression (CGI) Scale and self-rated PHQ-9. HAMD-24, a well-established representative scale for patient selection and follow-up assessments, has been selected to indicate the alteration in patients’ clinical symptoms both overall and in each subset item after treatment. When using this 24-item scale, a patient with the total score over 20 or higher will be considered to be suffering from moderate, severe or very severe depression [36–38]. This scale comprises 24 items indicating seven subsets includes: (1) anxiety/somatic symptoms; (2) weight alteration; (3) cognitive disorder; (4) diurnal symptom; (5) retardation; (6) insomnia; (7) helplessness and worthlessness and hopelessness [39]. The CGI is a 7-point scale, with a score based on the physician’s medical knowledge and experience regarding the patient’s general psychiatric condition. It includes the evaluation of the illness severity from 0 (normal) to 7 (the most severely ill) prior to therapy and two more aspects which are the therapeutic response and change from 1 (very much improved) to 7 (very much worse) after receiving medical treatment [40]. The Patient Health Questionaire-9 items (PHQ-9) is a self-reported questionnaire range from 0 to 27, each of the nine questions can be scored from 0 (not at all) to 3 (almost every day) according to the presence and severity of depression over past 2 weeks. It categorizes depression severity according to scores of 0–4 (none to minimal), 5–9 (mild), 10–14 (moderate), 15–19 (moderately severe) and 20–27 (severe) [41]. The Side Effects Rating Scale (SERS) of Asberg assesses the unwanted effects accompanied by antipsychotic drugs weekly, questions around the severity of increased fatigability, headache, insomnia, dizziness, orthostatic syncope, palpitations, tremor, increased tendency of sweating, reduced salivation, constipation, urination disorder, sleepiness, sexual dysfunction, and others. Its scores ranges from 0 (absent) to 3 (among the most severe) [42].

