### Secondary efficacy outcome measures

■ Changed quantitative value, obtained by subtracting the HAMD-24 score at each evaluation time point from the baseline score■ The changes in scores from baseline of other efficacy scales, such as the PHQ-9 and the CGI Scale

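### The primary efficacy formula gives improvement a negative reduction rate, opposite to the HAMD-24 secondary outcome, and has no value for a subset scored 0 at baseline

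*Protocol article*

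**What the plan says.** Under *Primary efficacy outcome measures* the protocol article applies the reduction rate to the HAMD-24 total and to each subset, and says that it "is defined as (Scores of each evaluation time point − baseline scores)/Baseline scores". The abstract uses the same label for the measure of efficacy: "The trends of efficacy will be evaluated by the reduction rate of the Hamilton Depression Rating Scale".

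Under *Secondary efficacy outcome measures* the absolute HAMD-24 change is "obtained by subtracting the HAMD-24 score at each evaluation time point from the baseline score", that is, baseline minus follow-up.

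The subsets are set out under *Study efficacy outcomes*: "This scale comprises 24 items indicating seven subsets includes: (1) anxiety/somatic symptoms; (2) weight alteration; (3) cognitive disorder; (4) diurnal symptom", followed by retardation, insomnia and a helplessness group. That section gives score ranges for the CGI, the PHQ-9 and the side-effect scale, but none for HAMD-24 items or subsets. *Inclusion criteria* require a HAMD-24 total of at least 20 and set no minimum for any subset.

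*Statistical analyses* plans an ANCOVA at each time point, adjusted for gender, age and baseline score. Missing efficacy values are filled by last observation carried forward, with a sensitivity analysis on the unreplaced data. Primary results follow intention to treat.

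**The concern.** There are two separate problems in one sentence of the plan.

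The first is direction. A measure called a reduction rate should rise as the patient improves. The printed formula does the opposite, and the absolute change on the same scale runs the other way. The article says that this sample is too small to show significant efficacy differences, and that the trends will inform the decision on a full-scale trial and its sample size. The direction and size of the estimates are therefore what the efficacy part delivers, and a label that contradicts its formula invites a reversed reading.

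The second is the denominator. A ratio to baseline is safe for the total, which is at least 20. It is not safe for a subset such as weight alteration or diurnal symptom, which may be absent in a patient who still qualifies on the total. The stated measure then has no value for that patient, and someone must choose a rule later, possibly with the data in view.

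**Working it through.** The plan states no figure to reproduce here, so the check evaluates its formulas.

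**Inputs from the protocol article**
- Primary: (follow-up − baseline)/baseline, for the total and each subset (*Primary efficacy outcome measures*).
- Secondary: baseline − follow-up (*Secondary efficacy outcome measures*).
- Baseline total at least 20, with no bound on subsets (*Inclusion criteria*).
- 14 patients enrolled per arm, 42 in all (*Sample size*, *Randomization and allocation concealment*).

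**Assumptions**
- A subset scores 0 when its symptoms are absent.
- The share p of patients with a zero baseline on a given subset is between 5% and 50%. The article gives neither figure.

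**Step 1: direction**

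| Baseline → follow-up | Primary as written | Secondary as written | (baseline − follow-up)/baseline |
|---|---|---|---|
| 30 → 15 | (15 − 30)/30 = −50% | 30 − 15 = +15 | +50% |
| 30 → 12 | (12 − 30)/30 = −60% | 30 − 12 = +18 | +60% |
| 30 → 36 | (36 − 30)/30 = +20% | 30 − 36 = −6 | −20% |

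The primary and secondary values have opposite signs whenever the score changes. Reversing the numerator makes them agree.

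**Step 2: does the sign affect the test?** Multiplying an outcome by −1 reverses every ANCOVA coefficient and leaves all sums of squares unchanged. The planned model, fitted to one simulated data set of 42 patients, gave F = 0.449 and p = 0.642 for the group effect with either sign. Only the direction of the estimate changes.

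**Step 3: zero baseline.** For a subset going 0 → 0 or 0 → 1, the denominator is 0 and the ratio does not exist, with either sign. Because baseline is the denominator at every visit, that patient has no defined value at any visit, so last observation carried forward has nothing to carry. The analysis of unreplaced data lacks the same values. The scores themselves are not missing; the formula fails on them.

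**Step 4: how many patients.** The expected number with a defined value per arm is 14 × (1 − p). The chance of at least one zero-baseline patient among 42, treating patients as independent, is 1 − (1 − p)^42.

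| Assumed p | Defined, of 14 per arm | Chance of at least one in 42 |
|---|---|---|
| 5% | 13.3 | 88% |
| 10% | 12.6 | 99% |
| 20% | 11.2 | >99.9% |
| 30% | 9.8 | >99.9% |
| 50% | 7.0 | >99.9% |

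So the case is likely to arise for a subset even at the low end of the range, while the number of patients lost depends heavily on p.

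**The case against.** The best defence is that the sign is a slip of labelling. The formula is printed, so the direction of every value can be recovered, and no response threshold, stopping rule or one-sided test in the article depends on it. This stands, and it limits the sign problem to labelling and interpretation.

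The second defence is that this is a feasibility and safety pilot with efficacy as a preliminary exploration, so no confirmatory claim is at risk. This also stands, and it lowers the severity.

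The third is that a rule for zero denominators is analysis-plan detail. This does not dispose of the point. The article fixes both the formula and its use on every subset, and that combination has no value for some patients. The objection is to a stated rule that fails, not to a missing one.

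The fourth is that a stated rule for zero baselines would be enough, without giving up the subset percentages. Such a rule would be a minimum repair. It would still have to leave those patients out or assign them an arbitrary value, and percentages of very small scores are coarse: 1 → 2 is +100% and 2 → 1 is −50%.

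A reader might go further and infer that patients drop out of the intention-to-treat analysis, or that new symptoms arising from zero are never counted. The article does not support either. Every patient has a total of at least 20 at entry, so the overall reduction rate and the absolute change can be calculated for anyone with scores. A subset rising from 0 to 2 adds 2 to the total and enters both. The loss is confined to that subset's own percentage comparison.

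**Conclusion.** The concern holds in two parts of different weight.

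- **Sign.** The formula contradicts its label and runs opposite to the HAMD-24 secondary outcome. This is certain from the text. It affects how the efficacy trends are read, and leaves F, p and the absolute size of any group difference as they are.
- **Subsets.** The ratio is undefined at every visit for a patient with a zero subset baseline, and neither planned approach to missing values repairs it. This rests on the assumption that a subset can score 0. The size rests on an assumed zero share with no anchor in the article: at 5% to 10% roughly one patient per arm is lost from that subset's comparison (13.3 or 12.6 of 14 remain), and at 50% half are lost (7.0 remain).

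The total-score analyses can be carried out as written, apart from the sign. Because efficacy is exploratory in this pilot, this should be fixed but does not undermine the trial.

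**What to change.** 1. Define the reduction rate as (baseline − follow-up)/baseline × 100%, and use it for the HAMD-24 total only, where the denominator is at least 20. It then has the same direction as the secondary absolute change.
2. Analyse each subset as its follow-up score, or as baseline minus follow-up, by the ANCOVA already planned, with that subset's own baseline as the covariate. Keep every patient with scores, including those at 0 at baseline.

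Reversing the sign alone is not enough, because it leaves the zero denominator in place. The change takes about two sentences and needs no new data. The cost is that subset results are no longer reported as percentages.

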### Secondary efficacy outcome measures

■ Changed quantitative value, obtained by subtracting the HAMD-24 score at each evaluation time point from the baseline score■ The changes in scores from baseline of other efficacy scales, such as the PHQ-9 and the CGI Scale

### Safety outcome measures

■ The physical examinations (including vital signs such as blood pressure, temperature, pulse, respiratory rate, system review of heart, lungs, gastrointestinal, central nervous system and psychiatric status) and SERS will be conducted on each evaluation time point. (see Fig. 2)■ Data from laboratory examinations, including routine blood and urine tests, serum biochemical tests (kidney function, liver function, proteins, iron status, and coagulation tests, as well as from instrumental examinations, such as electrocardiogram (ECG) and electroencephalogram (EEG), will be collected based on the schedule. (see Fig. 2)■ If any adverse events occur, physicians will document them on the adverse events report (AER) forms and on the CRF. The side effects will be documented on the CRF as well

**Fig. 2 Fig2:**
[figure not shown]
Participant timeline

### Participant timeline

See Fig. 2.

### Sample size

Considering that there are no previous studies from which to perform sample size calculation, and assuming drop-out rate less than 15%, we anticipate enrolling 14 patients per arm for a final sample size of at least 12 per arm [43]. Our collected data will aid in the calculation of the appropriate sample size for further large-scale study.

### Recruitment

Patients with MDD will be recruited 1 year at Zhujiang Hospital, Southern Medical University, from May 2017 to April 2018. Posters for recruitment will be posted in the in-/out-patient buildings of the hospital and in the Mental Health Center of Southern Medical University. Network advertisements will be issued in public via social media circles. Generally, participants will contact us and set appointments prior to the screening. Afterward, two assigned physicians will evaluate whether participants are eligible for our study following the inclusion/exclusion criteria and will provide detailed information about our study if qualified; otherwise, relevant medical advice will be offered.

### Randomization and allocation concealment

Forty-two patients will be randomized at a ratio of 1:1:1. A list of random numbers, generated by Statistical Analysis Software (SAS), version 9.2, using the permuted block-randomization method, will be used to assign the participants to one of the three treatment groups. The randomization codes will be sealed in consecutively numbered opaque envelopes. An independent bio-statistician will conduct the above procedure, and the envelopes will be locked in a cabinet. The key will be held by a research nurse. After a patient is included in our study, each envelope will be opened in ascending order by the research nurse and assign their treatment accordingly.

### Blinding

Referring to the randomization code, the research nurse will be aware of the patients’ treatment assignments and will prepare the drugs before administration. The research nurse will refrain from discussing the treatment assignment with both researchers and patients as mentioned in the confidentiality agreement. In addition, the clinical researchers, bedside nurses who dispense drugs and participants will be blinded. To achieve blinding, study drugs or placebo will be labeled with 0.9% saline (110 ml) regardless of their actual assignment while intravenous infusion. Reversal of blinding will be permissible under the emergency condition of severe adverse incidents; otherwise, un-blinding will be performed after our final database is locked.

### Data management and monitoring

The clinical researchers will receive 2 weeks of trial-related training regarding the research content and scale instructions prior to the start of our study. All researchers have completed their courses in Good Clinical Practice. The rater for the HAMD-24 pair, CGI scale, and SERS are licensed and experienced physicians with psychiatric learning backgrounds. The majority of HAMD-24 scale assessment data will be collected by face-to-face joint interviews, with one researcher using the structured interview guide to initiate discussion with the patients, while the other researcher obtains the missing required information if necessary and scores it separately afterward; this procedure is intended to increase the data reliability. After grading, if any controversial items appear, a consensus conference will be held or the patients may even be reassessed on the same day to improve data accuracy. Interviews through video teleconference will be used in some exceptional situations. The CGI scale data will be collected according to the available information through the interview with patient, care-giver, or daily observation while hospitalized. The SERS will be scored based on the information provided by the patients and excludes the symptoms of somatic anxiety from MDD. The self-rated scale PHQ-9 will ensure the patients’ full comprehension of each question in advance. Laboratory tests and instrumental examinations will be conducted in the relevant hospital department. Collected patient data will be recorded on the CRF by assigned clinical researchers. An independent Data Monitoring Committee (DMC) will meet after a group of six participants has completed their final visits to review the ongoing recruitment and protocol compliance, to safeguard the interests of the trial participants, to assess the safety and efficacy of the interventions during the trial and the consistency between the original data and CRF, to ensure that every adverse event is recorded on AER forms and that they are securely stored and to monitor the overall conduction of the clinical trial. An independent clinical research associate will prepare a final report for the principle investigators (PIs), [name] and [name] after the visit.

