### Harms

After initiating treatment, the participants will be encouraged to report any discomfort, and the physicians will record it on CRF and determine whether the discomfort is related to the study drugs. If any adverse events occurred, they will be documented on AER forms and entered into CRF, including the nature of the events, onset dates, causality with the study drugs, final diagnoses, severity, any given corrective managements, and clinical outcomes. Furthermore, physicians will provide expert care until the patients recover, the relevant expenses will be covered and financial compensation will be provided to patients through study funding. Severe adverse events will be reported to the hospital Ethics Committee, PI and sponsor within 24 h, and they will decide whether the study procedures should continue or cease based on the patients’ best interests.

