## Discussion

Multiple studies have revealed altered energy metabolism in brain regions. With the utilization of in-vivo phosphorous magnetic resonance spectroscopy, nucleoside triphosphate (NTP), which mainly derives from ATP, has shown to be decreased in depressed subjects [45]. Meanwhile, in MDD patients treated with either SSRI sertraline, or creatine, or thyroid hormones, which have been shown to increase brain bio-energetic metabolism, NTP levels are significantly increased in treatment responders compared with non-responders [26, 46, 47]. Compared with conventional ADs, novel compounds with fast-acting AD effects will minimize the time lag to obtain treatment results, enhance patients’ adherence, reduce the suicide rate and aid psychosocial recovery.

Our preclinical studies showed that ATP, as well as PCr, displayed rapid AD effects in animal models of depression. To our knowledge, our study is the first clinical attempt to add ATP/PCr intravenously with the orally administered fluoxetine to patients with moderate to severe MDD.

PCr, after being diluted in 0.9% saline 100 ml, should be infuse intravenously within the next 40 min. As this is a double-blinded experiment, both ATP and placebo group should be administered in less than 40 min. However, if the infusion rate of ATP is too fast, some patients might experience palpitations. We assume that the nocebo effects might influence the efficacy results in ATP group.

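### The SERS omits symptoms the rater puts down to somatic anxiety from MDD, so drug-caused palpitations, tremor or sweating can be under-counted on the trial's only side-effect rating scale

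*Protocol article*

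**What the plan says.** Under Data management and monitoring, the SERS is rated from what patients report, and the scoring "excludes the symptoms of somatic anxiety from MDD".

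Under Study efficacy outcomes, the symptoms listed for the SERS include "orthostatic syncope, palpitations, tremor, increased tendency of sweating". The same section names "1) anxiety/somatic symptoms" as one of the seven HAMD-24 subsets, without listing its items.

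Under Safety outcome measures, "SERS will be conducted on each evaluation time point", together with physical examinations. Laboratory tests, ECG, EEG and adverse event forms are listed beside it.

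The Discussion warns that "if the infusion rate of ATP is too fast, some patients might experience palpitations". Under Harms, physicians record any discomfort on the CRF and "determine whether the discomfort is related to the study drugs". Under Statistical analyses, safety data are summarised descriptively as relative frequencies.

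**The concern.** The exclusion has content only if some SERS items can also be somatic anxiety. Palpitations, tremor and sweating are plausible candidates. For each such symptom the rater must decide, in a single patient, whether it comes from the illness or from treatment, and leave it unscored in the first case. Every enrolled patient has moderate to severe MDD, so an explanation from the illness is always available.

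Randomisation already separates drug from illness through the comparison of arms. A judgement made before scoring adds nothing to that comparison, and wherever it is wrong it removes drug effect. Safety is one of the two stated aims of the pilot, the SERS is its only side-effect rating scale, and the rule touches the one ATP symptom that the authors name. Because the SERS will be reported as frequencies, an omitted symptom lowers the reported result directly.

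The point is the stated rule that makes the score depend on attribution. It is not that a condensed article lacks a rater manual.

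**Working it through.** **Plan's own figure.** The Sample size section enrols 14 per arm to keep at least 12, with drop-out below 15%. Losing 2 of 14 is 2/14 = 14.3%, so the statement is coherent. It is used here only as n = 14. The protocol gives no figure for palpitations or for misattribution.

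**Assumptions (not in the protocol).** True proportion of patients with palpitations: 30% on ATP and 10% on saline, or 20% and 5%. m is the share of affected patients whose palpitations are never scored because they are put down to MDD, taken as equal in both arms because raters are blinded.

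**Formulas.**
- Recorded rate = true rate × (1 - m).
- Recorded difference = true difference × (1 - m).
- Chance that no case is recorded among 14 ATP patients = (1 - recorded rate)^14.
- Chance of 3 or more recorded cases = upper binomial tail with n = 14.

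| True ATP / saline | m | Recorded ATP / saline | Difference (points) | P(none recorded on ATP) | P(3 or more on ATP) |
|---|---|---|---|---|---|
| 30% / 10% | 0 | 30% / 10% | 20 | 0.007 | 0.84 |
| 30% / 10% | 0.25 | 22.5% / 7.5% | 15 | 0.028 | 0.64 |
| 30% / 10% | 0.50 | 15% / 5% | 10 | 0.103 | 0.35 |
| 30% / 10% | 0.75 | 7.5% / 2.5% | 5 | 0.336 | 0.08 |
| 20% / 5% | 0 | 20% / 5% | 15 | 0.044 | 0.55 |
| 20% / 5% | 0.25 | 15% / 3.75% | 11.25 | 0.103 | 0.35 |
| 20% / 5% | 0.50 | 10% / 2.5% | 7.5 | 0.229 | 0.16 |
| 20% / 5% | 0.75 | 5% / 1.25% | 3.75 | 0.488 | 0.03 |

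For example, 0.30 × 0.5 = 0.15 and 0.85^14 = 0.103; 0.20 × 0.5 = 0.10 and 0.90^14 = 0.229.

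**What does not depend on the assumed rates.** Blinding stops attribution from differing through knowledge of the arm. It does not stop the dilution: any m above 0 shrinks a true difference, and m = 0 leaves it as it was. "None recorded" in the table means none on the SERS, not none in the trial.

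**The case against.** Several points on the other side stand.

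- **The text is narrow.** It excludes somatic anxiety that comes from MDD. It does not exclude palpitations as such, or drug-caused symptoms. The overlap with particular SERS items is an inference, though without some overlap the rule would do nothing.
- **Raters have information.** They are experienced physicians, researchers are trained for two weeks, and a rater could use presence before treatment and timing against the 08:00 and 16:00 infusions. Attribution need not be a coin-toss, so m may be small. The SERS is described as weekly, so a recurrent symptom would have to be misattributed each time to vanish.
- **Harms are captured elsewhere.** Any discomfort goes on the CRF, with relation to drug judged as a further step, and nothing says that unrelated discomfort is dropped. Adverse event forms, a cardiac system review with pulse and blood pressure at each evaluation, and scheduled ECG also run. The discomfort record depends on patients volunteering symptoms and does not correct the SERS frequencies, but the signal need not be lost to the trial.
- **The exclusion has a purpose.** A SERS total that includes depressive somatic symptoms falls as depression improves. If ATP worked, a larger fall in its total could mask side effects. This stands, and it shapes the fix.

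A reader might also infer three stronger things that the protocol does not support. First, that an omitted symptom moves into the HAMD-24: that scale is scored in a separate joint interview, and no text makes any of its items depend on what the SERS omits. Deleting the exclusion would leave it unchanged. Second, that the SERS is the main safety measure: it is the only side-effect rating scale, but it is listed with several other measures and none is ranked. Third, that palpitations are simply expected with ATP: the Discussion makes them conditional on too fast an infusion, and in some patients only.

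**Conclusion.** The point holds in a limited form. Scoring the SERS after attribution can under-count drug-caused symptoms that resemble somatic anxiety, and it shrinks both the SERS frequencies and the difference between arms by (1 - m). The direction follows from the rule, given that some attribution errors occur and that they do not favour one arm. The size cannot be determined from the protocol. Halving a 20-point difference is an illustration at an assumed m of 0.5, not an estimate. The effect is limited to the SERS results, in a pilot that reports safety descriptively without a test. No figure in the protocol is wrong on this point. The change is worth making because it is cheap and keeps all the information, not because the safety evaluation fails without it.

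**What to change.** Replace the exclusion with a rule that every SERS item is scored as the patient reports it, whatever its presumed cause, at baseline and at each visit. I could not see the schedule in Fig. 2, so check whether a baseline SERS is already planned.

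Add one CRF field per item for the rater's presumed cause (illness, study drug, other, uncertain), and state that it does not alter the score.

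Report, by arm and item, the number and percentage of patients with a new or worsened symptom relative to baseline, regardless of attribution. Give the table restricted by attribution as a supplement, so the analysis the authors intended is still available. Do not rely on change in the SERS total alone, because it also falls as depression improves. Item-level new or worsened symptoms are less exposed to this.

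The cost is a change of wording, one added type of CRF field and one further table. Raw SERS levels will be higher in all arms because symptoms of the illness are included. Recruitment of participants was ongoing when the article was written, so SERS forms already completed under the exclusion should be identified and shown separately if the omitted items cannot be recovered.
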